## Abstract

**Introduction:**

Emotion regulation difficulties have been associated with mental disorders and sexual dysfunctions. Traditional face-to-face transdiagnostic emotion regulation interventions have shown positive results for emotional and personality disorders. Only recently have the effects of these interventions on sexual health started to be investigated. Internet-delivered psychological interventions have several advantages over face-to-face interventions, such as cost-effectiveness, accessibility, and suitability for people who experience shame because of their stigmatized problematic behaviors and those who avoid seeking help. The aims of the SHER 2—TREpS (Portuguese acronym for Emotion Regulation training for sexual health) project are as follows: (a) determine the efficacy of an Internet-based emotion regulation intervention for sexual health and sexual satisfaction and (b) explore the effects of the intervention on (1) emotion regulation skills, (2) mental health, and (3) sexual self-perception.

**Methods and analysis:**

The study will use a randomized controlled trial design. Eligible participants will be randomly allocated to one of two groups: intervention (Internet-based emotion regulation training) or waitlist control. Assessments will take place before the start of the trial, at the end of the trial, and at 6-month follow up, after which participants assigned to the waitlist control condition will receive the same intervention. Primary outcomes include sexual function and satisfaction and secondary outcomes self-report measures of depression, anxiety, difficulties in emotion regulation, and sexual self-perception. This intervention study is financed by the Luxembourg National Research Fund (FNS).

**Ethics and dissemination:**

Ethics approval was obtained from the Ethics Review Panel of the University of Luxembourg. Findings will be disseminated via peer-reviewed publications and conference presentations.

## Strengths and limitations of this study

To the best of our knowledge, this is the first evaluation of an internet-based emotion regulation intervention for sexual health.The intervention protocol was developed encompassing both sex therapy and emotion regulation components already used for other mental disorders.Immediate and long-term (6 months) assessment of intervention effects on sexual health, mental health, and self-schema.

## Limitation

Participant assessments will be conducted via self-report questionnaires.Self-selection of participants.

## Introduction

Epidemiological studies suggest that 40–45% of adult women and 20–30% of adult men of the general population fulfill the criteria for at least one sexual dysfunction at one point in time during their lives [1]. Sexual dysfunctions (i.e., difficulties in the ability to respond sexually or to obtain sexual pleasure [2];) are multifactorial and involve physiological, affective, interpersonal, and psychological, context-related-factors [3]. They can only be understood by considering the constituent factors of sexual health, such as the experience and expression of thoughts, fantasies, desires, beliefs, attitudes, values, behaviors, and practices [4]. These factors may play a pivotal role in the development of sexual problems, and in maintaining sexual dysfunction in the long term [5].

One important factor is emotion regulation (ER), defined as the way in which emotions are generated, experienced, and used [6]. Such processes include emotional awareness (attention, differentiation, and labeling of emotions), expression (suppression versus expression of emotions), and experience (accessing and reflecting on one’s emotions and their consequences [6]). Emotion regulation difficulties have been associated with unhealthy coping strategies, mental disorders [7], and with difficulties in the sexual response cycle of both men and women (arousal, lubrication, orgasm, pain, erection and ejaculation [8, 9]).

A range of emotion regulation interventions have been shown as efficacious in the treatment of emotional and personality disorders, e.g., the Unified Protocol (UP [10]) and the Affect Regulation Training (ART [11]). In view of the high prevalence rates of emotion regulation deficits and comorbidity of sexual dysfunctions with other mental disorders [12], such interventions might also be helpful in treating sexual dysfunctions.

Recently, two studies tested an in vivo transdiagnostic approach to sexual problems. Parsons et al. [13] conducted a pilot study with 13 HIV-positive gay and bisexual men reporting high rates of sexual compulsivity. After up to ten intervention sessions, improvements were observed in all psychological outcomes, including sexual compulsivity, depression, and anxiety, as well as decreases in drug use and HIV risk behaviors. Nonetheless, the initial small sample size (*n* = 13) and the fact that only 4 participants completed all sessions limit the conclusions that can be drawn from these results. De Ornelas Maia et al. [14] conducted an intervention to enhance quality of life and sexual functioning in unipolar depressive disorder or anxiety disorder participants. Both intervention groups (UP group intervention + pharmacological treatment, and pharmacological treatment only group) showed significant improvements in quality of life, anxiety, and depression. Improvements in sexual functioning was also noticed; the effect size was larger for sexual dysfunction in the non-depressed group (*d* = 2.62) than in the depressed group (*d* = 1.04).

Although progress has been made in the psychological treatment of sexual problems, feelings of shame in meetings with physical face-to-face contact limit their dissemination. In contrast, internet-delivered interventions may offer a greater degree of perceived privacy and, therefore, appeal to those who otherwise would avoid seeking help. Additional advantages of internet-delivered interventions concern their cost-effectiveness and accessibility [15] and the possibility for patients to deal with their problem in their home environment [16].

Internet-delivered psychological interventions vary in the way they are delivered. They are usually composed of a package of comprehensive self-help material with which the patient receives information and exercises on a weekly basis [17]. The content is delivered in the form of text, video, or audio, which is presented on a platform together with homework assignments and interactions with a clinician and/or automated support functions (i.e., self-guided treatments). Overall, there is evidence that I-therapy is more effective than no intervention and, more importantly, similar in efficacy to face-to-face treatments [18].

Internet-delivered treatments have been applied in the area of sexual health care as well. Some studies have examined the effects of addressing sexual concerns using I-therapy. In a pilot study Van Diest et al. [19] tested an Internet-delivered protocol for different sexual dysfunctions and found improvements in sexual functioning in 67% of the participants (*N* = 39), with improvements maintained at 1-month follow-up. Van Lankveld et al. [20] found that treatment was superior compared to waitlist control in an Internet-delivered sex therapy for erectile dysfunction. Similarly, Andersson et al. [21] found that 7-week internet-delivered cognitive behavior therapy significantly improved erectile performance when compared to an online discussion control group.

Recently, two studies have been registered aiming at investigating the effects of I-therapy on sexual health, one comparing two Internet-based interventions (cognitive behavior therapy and mindfulness-based therapy) for the treatment of low sexual desire in women [22] and one analyzing the feasibility of a brief online psycho-educational intervention for sexual interest/arousal disorder [23]. However, there is a lack of studies examining the efficacy of Internet-delivered emotion regulation psychological interventions for sexual health.

## Aim

The first aim of the SHER 2—TREpS study is to determine the efficacy of an emotion regulation intervention for improving sexual health and sexual satisfaction.

The second aim is to explore the effects of the intervention on factors potentially mediating its effects, i.e., (1) emotion regulation skills, (2) anxiety and depression symptomatology, and (3) sexual self-perception (sexual self-schema and automatic thoughts during sexual activity).

### Research questions

In more detail, the following research questions will be addressed:
Does the TREpS intervention increase sexual health and sexual satisfaction?Does the TREpS intervention increase emotion regulation skills?Does the TREpS intervention decrease anxiety/depression symptomatology?Does the TREpS intervention improve sexual self-schema and decrease negative thoughts during sexual activity?

## Methods

### Design

A randomized controlled trial will be conducted. Participants will be allocated to either group 1 (intervention) or group 2 (waitlist).

Randomization will be performed prior to the enrolment of study participants. Two separate block randomization lists will be created (one per sex) via sealed envelope and participants with baseline completed will be allocated either on the TREPS intervention group or to a waitlist control group. The allocation will be conducted by a clinical psychologist with no involvement in the project and the intervention provider will have no influence on participants allocation. Analyses will be conducted and presented following the Consolidated Standards of Reporting Trials (CONSORT) statement [24, 25].

### Participants

#### Inclusion criteria

Individuals are eligible for participation if they meet the following criteria: (1) between 18 and 65 years of age, (2) fluent in Brazilian Portuguese, (3) self-reported sexual problems, assessed in men by a score of < 21 on the International Index Erectile Function (IIEF) and in women by a score of < 26 on the Female Sexual Function Index (FSFI), and (4) in a stable relationship for at least the preceding 3 months.

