#### Exclusion criteria

Volunteers will be excluded if they report (1) medical conditions that can interfere with the outcomes of the intervention, e.g., diabetes, cancer, cardiovascular problems, or (2) ongoing psychotherapy.

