### Recruitment

Recruitment will be conducted via the internet only. Advertisements concerning the project and invitations to take part in the study will be implemented using social media, targeting the Brazilian Portuguese speaking population. Additionally, participants of a previous online survey (SHER 1- study) who volunteered to participate in future studies will also be contacted.

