### Intervention

The intervention will involve an online emotion-regulation skills training for individuals with sexual problems. The protocol was developed based on existing emotion-regulation therapies [7, 10, 11, 45, 46]. It will last for 8 weeks, encompassing psycho-educational and emotion-regulation skills components. Every week participants will gain access to a different intervention module of the training, containing videos, presentation slides, written support material, and a recommendation of activities to be completed until the following week of training. Participants are expected to dedicate 30 min to 1 h per week to complete each module.

The intervention is structured as shown in Table 1.

**Table 1 Tab1:** Summary of intervention modules

	Module	Content
Week 1	Psycho-education on sexual function	Covers information about sexuality, sexual response cycle (desire, excitement, plateau, orgasm, resolution), and main difficulties that men and women may face in their sexual health, such as erectile dysfunction, premature ejaculation, desire disorders, pain disorders, and anorgasmia. It also differentiates the psychological characteristics of functional sexual response from a dysfunctional sexual response as well as the difference between sexual function and sexual satisfaction.
Week 2	Psycho-education on emotions and emotion regulation	Covers the definition of what emotions are, evolutionary aspects of emotions, emotion functions, emotion response cycles, emotion components (physical sensations, thoughts and behaviors), and long-term consequences of maintaining an emotional state for a longer period of time. It also defines pleasant and unpleasant emotions, the relationship between unpleasant emotion and avoidance behaviors, and avoidance strategies (emotional suppression, distraction and behavioral avoidance).
Week 3	Relaxation strategies: breathing and muscle relaxation	Informs about the common physiological response to anxiety and stress (e.g., increases in heart rate, respiration and muscle tension) and teaches two relaxation strategies: breathing relaxation and progressive muscle relaxation.

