Week 4	Cognitive flexibility	Refers to the rational component of emotion regulation. Aims to conceptualize and enhance cognitive flexibility, the triad situation-thought-emotion is explained and detailed through the concepts of what distinguishes thoughts and interpretations, what automatic thoughts and cognitive distortions are, and the identification of negative thought patterns and most common cognitive distortions related to sexuality are described.
Week 5	Non-judgmental awareness	Aims at teaching participants to experience their emotions in the present moment in a nonjudgmental way. The module also differentiates between experiencing an unpleasant emotion from experiencing an unpleasant emotion resulting from negative beliefs and reactions to experiencing it (snowball effect).
Week 6	Self-acceptance and compassion	Focuses on two psychological concepts necessary for a better emotion management: acceptance and self-compassion. These are important in order not to avoid emotional experiences and to diminish self-criticism associated with sexual difficulties.
Week 7	Emotion analysis	Presents a step-by-step flow-chart of how to identify emotions when experiencing them. By identifying emotions properly, we facilitate effective emotion regulation. The flow chart is composed of 6 items to pay attention when identifying an emotion: (1) emotion, (2) event-trigger situation, (3) evaluation/interpretation, (4) physical sensations, (5) previous similar experiences, and (6) behavior.
Week 8	Sexual emotional exposures	Makes a summary of all previous modules and suggests a series of sexual experiences paying attention to the emotions experienced during the activities (exposures). Such gradual approach diminishes the risk of intense emotions and avoidant behaviors. By succeeding on the exposures, obtaining pleasure on the activities, assessments of danger/discomfort diminish and more adaptive evaluations arise, facilitating the identification and modification of emotional behaviors.

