### Control

The control group will not receive any intervention during the trial but will be offered the same treatment at the end of the 6 months follow-up assessment (waitlist-control).

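### Nothing stops both partners of a couple from enrolling and landing in opposite arms, so a waitlist control may share a partner's training; the effect is probably small and cheap to prevent

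*Protocol article*

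**What the plan says.** All references are to the protocol article.

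- **Inclusion criteria.** The unit is the person: "Individuals are eligible for participation if they meet the following criteria". One criterion is being "in a stable relationship for at least the preceding 3 months". Another is a score below 21 on the IIEF for men or below 26 on the FSFI for women.
- **Exclusion criteria.** The list opens "Volunteers will be excluded if they report (1) medical conditions that can interfere with the outcomes of the intervention" and has one further entry, ongoing psychotherapy. The registration dataset (Table 2, item 13) repeats the criteria and adds no rule about partners.
- **Recruitment.** "Recruitment will be conducted via the internet only", by social-media advertising and by contacting volunteers from an earlier survey. Both sexes are sought (Sample size: 102 per gender).
- **Design.** "Two separate block randomization lists will be created (one per sex"), and people are allocated once their baseline is complete. Couples are not identified, linked or allocated together.
- **Control.** "The control group will not receive any intervention during the trial".
- **Intervention.** Weekly modules "containing videos, presentation slides, written support material, and a recommendation of activities to be completed until the following week of training". In Table 1, Week 8 "suggests a series of sexual experiences paying attention to the emotions experienced during the activities (exposures").

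**The concern.** The relationship criterion means that every participant has a partner within reach of the same advertisements. The training is used at home, and its final module concerns sexual activity. The primary instruments cover sexual function and satisfaction within what may be the same relationship.

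If one partner is in TREpS and the other is on the waitlist, the control may see the materials, try the activities or share the suggested experiences. That person then no longer represents the untreated condition described under Control. The expected consequence is a contrast biased toward no difference, and the sample-size statement makes no visible allowance for it.

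The article describes no procedure for finding such pairs afterwards. The identifier key list holds addresses, but no matching is planned and the list is to be destroyed once the trial ends.

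**Working it through.** **Inputs from the article.** Individual 1:1 allocation; α = .05; power .80 or greater; 51 per arm (102), doubled to 204, which is 51 per arm within each gender. The article gives no effect size, no block size and no figure for couples or contamination.

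**Assumed inputs.** q is the share of participants whose partner is also enrolled. s is the fraction of the treatment effect that reaches a control whose partner is in TREpS.

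**Step 1: chance that a couple is split.** For a man and a woman on two independent 1:1 lists:

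P(opposite arms) = 2 × 0.5 × 0.5 = 0.50.

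For two people on the same list the chance is also about 0.5. It is higher if both fall in the same block of size b, where it is b / [2(b − 1)]: 4/6 = 0.67 for b = 4 and 6/10 = 0.60 for b = 6 (block sizes assumed).

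**Step 2: attenuation.** Half of the controls with an enrolled partner have that partner in TREpS, so the exposed share of controls is q/2. The contrast is multiplied by 1 − s × q/2, and the attenuation is s × q/2.

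**Step 3: the plan's own figure.** With no effect size stated, 51 per arm can only be solved backwards. With a two-sample t-test at 80% power, 51 per arm corresponds to a standardised difference of about 0.56 two-sided; one-sided, a difference of 0.50 gives exactly 51. The two-sided case is used below as a reference point only.

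**Step 4: effect on power and sample size.** Power is for 51 per arm at a difference of 0.56 × (1 − s × q/2). The number needed is 51 / (1 − s × q/2)², rounded up. Couples among 204 participants = 204 × q/2.

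| q | Couples in 204 | s | Attenuation | Power | Needed per arm |
|---|---|---|---|---|---|
| 5% | about 5 | 0.5 | 1.25% | 79% | 53 |
| 5% | about 5 | 1 | 2.5% | 78% | 54 |
| 10% | about 10 | 0.5 | 2.5% | 78% | 54 |
| 10% | about 10 | 1 | 5% | 76% | 57 |
| 20% | about 20 | 0.5 | 5% | 76% | 57 |
| 20% | about 20 | 1 | 10% | 71% | 63 |
| 40% | about 41 | 0.5 | 10% | 71% | 63 |
| 40% | about 41 | 1 | 20% | 61% | 80 |

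For example, at q = 20% and s = 0.5: 0.5 × 0.20/2 = 0.05, and 51 / 0.95² = 56.5, so 57.

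**Step 5: with one participant per couple.** q becomes 0, the attenuation is 0, and no inflation is needed for this reason.

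**The case against.** The strongest reply is that this is a silence about a subgroup that may hardly exist. Both partners must volunteer separately, each must score below the relevant cut-off, and neither may have an interfering medical condition or be in psychotherapy. The Introduction presents internet delivery as suited to people who value privacy, which does not suggest many joint enrolments. An attenuation of 10% at s = 50% would need 40% of all participants to be in enrolled couples, and nothing in the article supports that. Couples who are both in TREpS might also gain more than single participants, which would offset some of the dilution. All of this stands, and it is why the point is a low-cost improvement and not a serious flaw.

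It may also be said that an article condenses a fuller protocol, where such a rule could sit. That is possible. But the criteria are given as numbered lists and repeated without the rule in the registration table, and an eligibility criterion is not a detail normally left to an analysis plan.

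Three stronger readings are tempting and should not be drawn:

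- **That the separate lists per sex cause the problem.** They do not. A single individual-level list would also split about half of couples (Step 1). The cause is the absence of a one-per-couple rule.
- **That a control is directly exposed or takes part in the treatment.** Table 1 says that Week 8 suggests experiences. It gives the partner no role, and it is one module of eight. Materials sit behind an individual login, although that control is described for confidentiality. Spillover is a plausible inference and not something the article states.
- **That correlated partners invalidate the analysis of variance.** The FSFI and IIEF are sex-specific, so opposite-sex partners never meet in those analyses. The Data analysis section does not say that the sexes are pooled for other outcomes. Even if they were, with within-couple correlation ρ, couples in the same arm scale the variance of the group difference by 1 + ρ and split couples by 1 − ρ. With half of each, the average is 1.

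**Conclusion.** The point holds as a gap in the eligibility rules. The criteria as written let both partners enrol, and individual allocation then puts them in opposite arms about half the time. A control in that position may share the training, which would pull the contrast toward no difference.

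The magnitude cannot be established from the article. Under assumed values it runs from about 1% of the effect (q = 5%, s = 50%) to 5% (q = 20%, s = 50%). The first would move power from 80% to 79%, the second to 76%. Larger losses need couple shares that look unlikely under these criteria. The direction assumes that spillover to controls outweighs any extra gain among couples who are both in TREpS. No figure stated in the plan is shown to be wrong.

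**What to change.** Add one exclusion criterion: a partner already enrolled in this trial, so that each couple contributes one participant. Apply it with one yes/no item in the online baseline form. Since allocation follows the completed baseline, the answer is available before anyone is assigned.

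The registration table gives the status as enrolling. Put the same item to those already in the trial, use it to flag couples, and prespecify a sensitivity analysis without them. That analysis should drop flagged pairs whatever their arms; dropping only the exposed controls would remove people from one arm alone.

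The cost is one eligibility line, one form item, the ethics approval and notification that the article requires for protocol changes, and a few otherwise eligible volunteers turned away. The item relies on self-report and will miss someone who does not know that the partner has enrolled.
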